All techniques/approaches will be delivered via the exercise therapists and protocoled, supported and guided by the ImPuls App.

*Item 11b Criteria for discontinuing or modifying allocated interventions for a given trial participant (eg, drug dose change in response to harms, participant request, or improving/worsening disease)*

Participants who miss more than 4 sessions in a row (of w0 to w4; supervised-phase) of the intervention (≥40%, due to any reason) but continue the study assessments are defined as **treatment-dropout**, since they did not receive the intended dose of the intervention. They can still participate in the remaining sessions of the intervention and will be asked to complete all remaining assessments. Participants who miss more than 4 sessions in a row (of w0 to w4; supervised-phase) of the intervention (≥40%, due to any reason) and discontinue the study assessments are defined as **study-dropout**. All participants agree to be asked to specify their reasons for study/treatment-dropout on a voluntary basis (once, after treatment/study-dropout). Reasons for discontinuation will be reported.

If more than 50% of participants discontinue their participation in the intervention group during the first five weeks (w0 to w4) of the delivery, discontinuation of the group due to lack of economic efficiency for the study sites is possible. If only one participant of the intervention group remains, he or she can no longer receive the intervention, since delivery of the intervention to less than two participants no longer qualifies as “group-based intervention”.  All participants, including drop-outs, will be asked to complete all of the following study assessments on a voluntary basis.

*Adherence*

*Item 11c: Strategies to improve adherence to intervention protocols, and any procedures for monitoring adherence (e.g., drug tablet return; laboratory tests).*

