#### **Health related quality of life.** Health related quality of life will be assessed by the German version of the EQ-5D-5L questionnaire (Herdman et al., 2011; Hinz et al., 2014). It consists of five items concerning the domains mobility, self-care, usual activities, pain or discomfort and anxiety or depression with five answer alternatives each (range: 1-5). The combinations of the answer alternatives can be described with a five-digit number (i.e. the pattern 11111 indicates the optimal health state). Through the EQ-5D-5L questionnaire Quality Adjusted Life Years (QALY) are captured for the economic evaluation. The EQ-5D-5L has an internal consistency of Cronbach’s α = .86 among German chronic heart failure patients. Current data concerning internal consistency in patients with mental disorders exists for the Spanish version of the EQ-5D-5L. Among Spanish patients with major depression the EQ-5D-5L has an internal consistency of Cronbach’s α = .77 (Bilbao et al., 2021).

**Routine data of the health insurances/health care costs**. For the economic evaluation, patients’ routine data collected 6 months before the intervention, during the time of the intervention, and six months after the intervention will be provided by the two participating statutory health insurers (AOK and TK). This data will include patients’ master data, such as gender and age, as well as patient treatment costs. Parameters for treatment costs will comprise costs of inpatient and outpatient care as well as medication, medicals aids or days of incapacity to work. Routine data for each patient will be provided for the time of the intervention as well as one year prior and one year after. The relevant costs are assessed and aggregated as quantities. In addition, cost parameters resulting from the intervention and the implementation will be considered. Subsequently, routine insurance data will be linked to primary data collected.

**Change of health insurance during study participation.** In the case of a change of health insurance company during the study participation, the corresponding participant is still part of the study and continues to complete the assessments. However, routine data of the health insurances/health care costs cannot be provided.

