### Assessments to ensure internal validity

***Symptom severity at randomization.*** Symptom severity might change or fluctuate from the diagnostic interview or pre-assessment to the start of the intervention. In order to ensure clinically relevant transdiagnostic and disorder-specific symptomatology with the start of the intervention, scales that assess all primary and secondary outcomes will be presented again between randomization and group start: BSI-18 (Derogatis & Fitzpatrick, 2004), ISI (Dieck et al., 2018; Morin, 1993), PSQI(Buysse et al., 1989), PHQ-9 (Kroenke et al., 2001; Spitzer et al., 1999), GAD-7 (Lowe et al., 2008; Spitzer et al., 2006), PCL-5 (Kruger-Gottschalk et al., 2017).

**(Serious) Adverse Events.** Adverse events (AE) will be assessed at pre, post-1, and follow-up assessment. AEs and Serious Adverse events (SAEs) can be further reported by patients or therapists at a central phone number. AEs and SAEs will be documented and SAEs will be reported to an independent Data Safety and Monitoring Board, which will discuss adjustments to or discontinuation of the entire study**.**

**~~Treatment Fidelity (adherence to protocol of study therapists).~~** ~~Core elements of the manualized ImPuls intervention have been determined a priori. All inhouse sessions (see fig. 3 and table 1) of all therapists at all study sites will be video-taped despite outdoor MVAE. External research assistants will be trained to rate fidelity based on deliverance as intended in the manual. A treatment fidelity score will be determined as a mean of all ratings. 10 % of all video-taped sessions will be randomly selected and analyzed. A fidelity score of ≥ 90 % is assumed~~.

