**Dropout and attendance rates (patients).** A drop-out rate less than 30 % and attendance rate ≥ 80 % is assumed. Attendance within the supervised (weeks 0-4; please refer to fig. 3) and partially supervised (weeks 5-24) period will be assessed via the ImPuls smartphone application and attendance lists by the exercise therapists/study site. Participants who miss more than 4 consecutive sessions during the four weeks of the supervised phase (of weeks 0-4) of the intervention (≥40%, due to any reason) but continue the study assessments are defined as treatment-dropout, since they did not receive the intended dose of the intervention. They can still participate in the remaining sessions of the intervention and will be asked to complete all remaining assessments. Participants who miss more than 4 consecutive sessions during the four weeks of the supervised phase (of weeks 0-4) of the intervention (≥40%, due to any reason) and discontinue the study assessments will be defined as study dropout. Participants who will discontinue the treatment as well as the assessments will be defined as study dropout. All participants agree to be asked to specify their reasons for study/treatment-dropout on a voluntary basis (once, after treatment/study dropout). If available, reasons for discontinuation will be reported. If more than 50% of participants will discontinue their participation in the intervention group during the first five weeks (weeks 0-4) of the delivery, discontinuation of the group due to lack of economic efficiency for the study sites is possible. If only one participant of the intervention group remains, he or she can no longer receive the intervention, since delivery of the intervention to less than two participants no longer qualifies as “group-based intervention”.

**MVAE dose within the supervised period (patients).** Frequency (at least twice a week), intensity (mean intensity of least 64 % of maximum heart rate) and duration (at least 30 minutes of MVAE in each session) of exercise during the supervised period (weeks 1-4) will be assessed via the ImPuls smartphone application.

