## Data Collection Methods

*Item 18a: Plans for assessment and collection of outcome, baseline, and other trial data, including any related processes to promote data quality (e.g., duplicate measurements, training of assessors) and a description of study instruments (e.g., questionnaires, laboratory tests) along with their reliability and validity, if known. Reference to where data collection forms can be found, if not in the protocol.*

Please refer to *item 11 d* **“Outcomes”**

*Item 18b: Plans to promote participant retention and complete follow-up, including list of any outcome data to be collected for participants who discontinue or deviate from intervention protocols.*

In accordance with the Evaluation Concept and Record of Processing Activities, all data for evaluation runs through REDCap on a secured LMU internal server providing a stable and traceable coding, storage and security structure as well as data quality measures such as automatic survey reminders, alerts to researchers for telephone reminders to participants, and data type and range checks where appropriate. Missing values on surveys have to be confirmed by participants to be intentional before being able to proceed to the next questionnaire.

The process evaluation data collected via app are stored pseudonymously on a server of the Central Office of the University of Tuebingen (Tue-CO) and transmitted pseudonymously to LMU-Psy. Likewise, videos of the group sessions will be recorded by Tue-MA as part of the process evaluation. These videos will be stored on a hard-drive at the Tü-CO and transferred to the LMU-Psy via RedCap. The routine data of the health insurances (AOK/TK) include outpatient, inpatient, as well as medicines, remedies and aids six months prior and up until six months after completion of the intervention period and are transmitted to the trust center (TUM-TC) on the basis of a pseudonym assigned by the Tue-CO, which is not known to the patients, and from there double pseudonymized to the TU Munich (TUM-HSM). The data stored at LMU-Psy (primary and secondary endpoints, data on progression diagnostics and process evaluation) are transmitted to TUM-TC via a secure connection. From there, they are transmitted to TUM-HSM with the routine data and will be double pseudonymized.

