## Harms

*Item 22: Plans for collecting, assessing, reporting, and managing solicited and spontaneously reported adverse events and other unintended effects of trial interventions or trial conduct.*

Adjustments to the study or discontinuation of the entire study will be discussed regularly with the independent Data Safety and Monitoring Board in light of reported Adverse Events (AE) or Serious Adverse Events (SAE).

Adverse events (AE) describe any deterioration in the mental or physical condition or behavior of a participant administered the intervention, including events not necessarily caused by or related to the intervention. Following this definition, the following categories are defined as AE for the purposes of this project:

- Onset of new psychological symptoms
- Significant worsening of pre-existing psychological symptoms
- Occurrence of new physical symptoms
- Significant worsening of pre-existing physical symptoms
- Injuries that result in not being able to perform any sports activity for at least 2 months
- Covid-19 infections

A serious adverse event (SAE) is any adverse event that results in death, is life-threatening, requires inpatient hospitalization or prolongation of an existing hospital stay, or results in persistent or significant disability/incapacity. Other significant events may also be considered serious if they endanger the participant or require interventions to prevent any of the above mentioned consequences. Consequently, the following events are considered SAE under this project:

- Suicide
- Suicide attempt
- Other event that resulted in death
- Intentional serious self-injury that resulted in an inpatient stay
- Third party injury
- Event that is acutely life-threatening (i.e., study participant is in acute danger of death)
- Event that results in significant physical disability
- Hospitalization due to psychiatric and somatic symptoms

The above-mentioned categories of AE are recorded during the structured assessments (post, follow-up) via online questionnaires. In addition, participants and therapists (in the case of spontaneous reports by patients) have the opportunity to report AEs to a study telephone (available daily from 9 a.m. to 5 p.m.) at the central office at the University of Tuebingen. Employees of the study center document AEs in a CRF.

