Based on the above list, SAEs are recorded by the exercise therapists during the intervention phase and reported to employees of the central office of the University of Tuebingen. In addition, SAEs will be collected by employees of the University of Tuebingen at all three measurement time points (pre, post, follow-up) for the intervention and control groups. They then report SAEs to the study director ([name]), who consults an independent Data and Safety Monitoring Board for further action within 12 hours after the SAE. The Data Safety and Monitoring Board is composed of independent researchers who are not associated with the project but have expertise in clinical or medical research. All members of the Data Safety and Monitoring Board are listed above. The Data Safety and Monitoring Board decides within 24 hours on any actions that may be necessary (e.g., changes in the trial or similar) and passes these on to the study director. All information on AEs and SAEs will also be recorded in the RedCAP system, like all other data collected.

The following data is documented for each AE/SAE:

- Pseudonym of participant
- Study site to which the participant was associated
- Date of start of SAE and associated study phase (pre, intervention phase, post or follow-up)
- Description of the SAE
- information on whether there was a risk for other participants
- Severity (rated by PI and DSMB)
  - **Mild** – Events require minimal or no treatment and do not interfere with the participant’s daily activities.
  - **Moderate** – Events result in a low level of inconvenience or concern with the therapeutic measures. Moderate events may cause some interference with functioning.
  - **Severe** – Events interrupt a participant’s usual daily activity and may require systemic drug therapy or other treatment. Severe events are usually potentially life-threatening or incapacitating. Of note, the term “severe” does not necessarily equate to “serious”.
- relationship to study intervention (rated by PI and DSMB)
  - **Related** – The AE is known to occur with the study procedures, there is a reasonable possibility that the study procedures caused the AE, or there is a temporal relationship between the study procedures and the event. Reasonable possibility means that there is evidence to suggest a causal relationship between the study procedures and the AE.

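### Hospitalisation SAEs rest on reports alone, with unequal surveillance between arms, while linked inpatient claims for both arms are assigned only to the economic evaluation

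*Protocol*

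**What the plan says.** Harms (Item 22) includes "Hospitalization due to psychiatric and somatic symptoms" in its list of serious adverse events (SAEs). The protocol gives three routes by which an SAE reaches the record:

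- Therapists: "SAEs are recorded by the exercise therapists during the intervention phase and reported to employees of the central office" (Harms).
- Study staff, in both arms: "SAEs will be collected by employees of the University of Tuebingen at all three measurement time points (pre, post, follow-up" (Harms).
- Telephone: "AEs and Serious Adverse events (SAEs) can be further reported by patients or therapists at a central phone number" (Assessments to ensure internal validity).

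Data Management (Data Entry) fits this picture: staff enter adverse event data once a therapist or participant has notified them.

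A study-dropout is someone who has stopped both treatment and assessments (Item 11b; Dropout and attendance rates). Item 11b adds that all participants, drop-outs included, "will be asked to complete all of the following study assessments on a voluntary basis". On the extent of dropout, the protocol states: "A drop-out rate less than 30 % and attendance rate ≥ 80 % is assumed". The Sample Size section (Item 14) uses 30%.

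On claims, Data Collection Methods (Item 18b) states: "The routine data of the health insurances (AOK/TK) include outpatient, inpatient, as well as medicines, remedies and aids six months prior". The paragraph on routine data under Secondary Outcomes promises these data for each patient and adds: "Subsequently, routine insurance data will be linked to primary data collected". The stated purpose is the economic evaluation. Nothing in the protocol assigns the claims to harms.

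**The concern.** Every SAE route needs a patient, a therapist or a staff contact to produce a report. The scheduled collection at post and follow-up is exactly the contact that a study-dropout has given up. An admission in such a patient may never be recorded.

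Surveillance is also unequal by design. ImPuls patients have a therapist who records SAEs and telephones them weekly and then biweekly to week 24. TAU patients have no such person. This tends to raise recorded events in ImPuls, whereas higher dropout in ImPuls, if it occurred, would lower them. A reported arm comparison of hospitalisation SAEs would then be hard to interpret.

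The inpatient claims do not depend on survey response and come from the same source in both arms. Hypothesis 2 compares overall costs between conditions, and inpatient care is one component, so inpatient use by arm is needed anyway. Without a stated link, the trial could publish claims-based inpatient use and report-based hospitalisation SAEs that disagree, with no explanation.

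**Working it through.** **The planning figure.** Sample Size gives d = 0.348, two-sided alpha 0.05, power 80% and 30% dropout. The two-sample t-test needs 131 per arm, 262 in total, and 262/0.70 = 374.3, rounded up to 375. The protocol's figure reproduces, and 30% is applied as an overall allowance. At the target of 600 it corresponds to 0.30 × 600 = 180 patients.

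**Share of hospitalised patients missed.** Let d be dropout, r the admission risk of dropouts relative to completers, and c the proportion of dropouts' admissions still captured by a report. Then

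share missed = d·r·(1 − c) / [(1 − d) + d·r].

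Only d = 0.30 comes from the protocol; r and c are assumptions.

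| r | c = 0 | c = 0.5 |
|---|---|---|
| 1 | 0.30/1.00 = 30% | 0.15/1.00 = 15% |
| 2 | 0.60/1.30 = 46% | 0.30/1.30 = 23% |
| 3 | 0.90/1.60 = 56% | 0.45/1.60 = 28% |

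The protocol gives no hospitalisation risk. For N = 600, r = 1 and assumed 12-month risks of 2%, 5% and 10%, the expected numbers hospitalised are 12, 30 and 60. Of these, 3.6, 9 and 18 are missed with c = 0, and 1.8, 4.5 and 9 with c = 0.5.

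**Arm comparison.** Assume equal true risk, r = 1 and all randomised patients as denominator. The recorded risk ratio (ImPuls/TAU) is [(1 − d₁) + d₁c₁] / [(1 − d₂) + d₂c₂]. All imbalances below are assumed.

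- Equal dropout and equal capture: 1.00.
- Dropout 30% v 15%, no capture: 0.70/0.85 = 0.82.
- Dropout 40% v 20%, no capture: 0.60/0.80 = 0.75; reversed, 1.33.
- Dropout 30% in both arms, capture 50% in ImPuls (through therapists) and 0% in TAU: 0.85/0.70 = 1.21.

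The direction therefore depends on which imbalance dominates.

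**Denominator.** Take 300 per arm, an assumed true risk of 8%, dropout 30% v 15% and no capture. Completer risk is 0.08/[(1 − d) + d·r], and there are 210 and 255 completers.

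| r | Completer risk | Recorded | Ratio, all randomised | Ratio, assessed only |
|---|---|---|---|---|
| 1 | 8.00% v 8.00% | 16.8 v 20.4 | 0.82 | 1.00 |
| 2 | 6.15% v 6.96% | 12.9 v 17.7 | 0.73 | 0.88 |
| 3 | 5.00% v 6.15% | 10.5 v 15.7 | 0.67 | 0.81 |

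The protocol states no harms denominator, so neither column can be called the trial's own result.

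**Claims window.** The routine-data paragraph gives six months before and after the intervention, then one year before and after it; Item 18b gives six months. Both versions cover roughly the 12 months after randomisation, apart from margins at the start and end. For TAU patients, who have no intervention, the anchor date needs stating.

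**The case against.** The case for leaving the plan alone has weight. Collecting SAEs through staff inquiry, therapists and a telephone line is coherent and contradicts nothing. Drop-outs are still asked to complete assessments, and central staff telephone non-responders (Item 11c). Therapists also call absent patients and stay in telephone contact to week 24. Zero capture is therefore an extreme case, least plausible in ImPuls. The 30% is a sample-size allowance, not a forecast of patients without SAE data. How harms are tabulated can properly be left to the SAP. All of this stands, and it limits what can be claimed.

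A reader might infer that dropouts' admissions are lost outright, or that ImPuls will look safer than it is. The documents support neither. The first ignores the continued contact; the second needs assumed unequal dropout and an all-randomised denominator, and ignores the extra surveillance in ImPuls.

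A reader might also infer that claims should replace the reported count. They cannot:

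- Any admission is broader than the listed SAE and includes planned or unrelated stays.
- Claims carry none of the severity, relatedness and expectedness ratings that Harms requires.
- The protocol describes cost parameters aggregated as quantities and does not promise discharge diagnoses.
- SAE records are not named among the data sent to the trust center.
- Claims are unavailable after a change of insurer, and nothing says whether delivery continues after withdrawal.

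What the objection does not remove is that the protocol itself fixes the sources of harms data. They are all report-based and unequal between arms, while a source independent of survey response is already being obtained.

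**Conclusion.** The point holds as a weakness in ascertainment, not as an error of calculation or a contradiction in the SAE rules; no sample size or power figure changes. Hospitalisation SAEs in patients who stop assessments may be missed, and surveillance differs between arms even without dropout. At 30% dropout and equal risk, between 15% (half capture) and 30% (no capture) of hospitalised patients would go unrecorded. The share is larger if dropouts are at higher risk and smaller if dropout stays below 30%, as the protocol expects. Any distortion of the risk ratio rests on assumed differences in dropout or capture and on the denominator, so its direction and size cannot be stated from the documents. A supplementary use of the claims is worth making because it costs little.

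**What to change.** Add to Item 22 a supplementary retrospective table of all-cause inpatient admissions from the insurance claims. It should be by arm, from randomisation to month 12, in all randomised patients with claims data, whether or not they completed assessments. Label it as all-cause admissions and place it beside the reported hospitalisation SAEs, without replacing them. Report the number without claims in each arm. Split by psychiatric and somatic diagnosis, or show agreement with reported SAEs, only if diagnoses and SAE records are in the linked data.

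Before that:

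- Reconcile the claims window (six months against one year) and state the anchor date for TAU patients.
- Confirm that consent and the data-protection concept cover this use.

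Event-by-event reporting to the Data Safety and Monitoring Board stays as it is.

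The cost is one table from data already obtained for the economic evaluation, possibly with an addition to the data-protection concept. Claims arrive late and so serve only the final comparison, insurer switchers are missing, and planned or unrelated admissions are counted. The decision should come early enough for the data to be available, since Data Management has the trust center's data erased one year after study completion.
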